### Research and Innovation Questions

This innovative project will include 5 key research questions (RQs), which we propose will fill in the gaps in our current knowledge.

RQ1 (WP2) is as follows: In people with MS, what is the usability and feasibility of an advanced telerehabilitation system in facilitating remote exercise training? Qualitative and quantitative measures will be used to evaluate the usability and feasibility of the telerehabilitation system in 4 countries. Following necessary system upgrades and adaptations, findings will be incorporated into the feasibility multicenter RCT (WP4). Based on data from other patient populations, we hypothesize that the innovative telerehabilitation system will score highly for usability and feasibility among the participants with MS.

RQ2 (WP3) is as follows: In people with MS, are scores provided by clinical mobility tests obtained via tele-rehabilitation valid and reliable? Evidence for remote mobility evaluation does not currently exist for people with MS. We will evaluate 5 tests developed from commonly used clinical measures. We hypothesize that innovative remote mobility tests will demonstrate good-to-excellent validity and reliability.

RQ3 (WP4) is as follows: In people with MS, is a large multicenter RCT possible, and can it show preliminary efficacy of an individualized exercise program delivered via telerehabilitation to improve mobility compared with in-person physical therapy? An international pragmatic multicenter feasibility RCT will be conducted to compare the effectiveness of delivering the individual exercise program via telerehabilitation versus in person by a physiotherapist. We hypothesize that both exercise intervention programs will improve mobility in people with MS; however, nonsignificant differences in mobility outcome measures between groups (telerehabilitation vs usual care) will be demonstrated.

RQ4 (WP4) is as follows: In people with MS, does an individualized exercise program delivered via telerehabilitation have a comparable effect on mood and quality of life (QoL) compared with standard physical therapy (facility based)? This RQ will be answered in the planned international multicenter feasibility RCT, preceded by a feasibility and usability study. Consequently, our hypothesis is that mood and QoL will be improved in participants whose symptoms are significant at baseline.

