### Outcome Measures for the Feasibility Multicenter RCT

The outcome measures for WP4 will include the 30STS [36] (primary outcome), SPPB [37], 6-minute walk test (6MWT) [38], timed 25-foot walk test (T25FWT) [39], mini-BESTest (balance) [40], FRT [41], and a self-report questionnaire, the 12-item MS Walking Scale (MSWS-12) [42]. In accordance with the project’s secondary aims, we will examine the impact of the intervention programs on mood (ie, depression and anxiety with the State-Trait Anxiety Inventory [STAI] [43] and Quick Inventory of Depression Symptomology [QIDS] [44]), quality of life (EQ-5D-5L [45]) and the impact of MS (29-question Multiple Sclerosis Impact Scale; MSIS-29 [46]).

All outcome measures will be collected at baseline (at the initiation of the intervention program), and after the intervention period’s completion. Assessors (physical therapists) will be blinded to group allocation, and patient report outcomes will be collected using an online form. Other significant disease-related factors collected solely at baseline (together with demographic and relevant clinical information) will include perceived fatigue (Modified Fatigue Impact Scale; MFIS [47]) and cognition (Symbol Digit Modality Test; SDMT [48]). Additionally, we will collect baseline information on digital literacy, which may confound the intervention’s effectiveness. All outcome measures used for the study have been validated in people with MS and are recommended for rehabilitation and clinical trials.

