### Data Analysis and Statistical Plan

Each research question is addressed through specific outcome measures. For RQ1, usability and feasibility will be assessed via the TUQ, adherence rates, dropout rates, and stakeholder interviews, with qualitative data analyzed thematically. RQ2 involves psychometric evaluation of remote assessments (e.g., SPPB, STS, and TUG) using intraclass correlation coefficients for test-retest reliability and Pearson correlations to compare remote and in-person scores. RQ3 and RQ4 outcomes (eg, 30STS, MSWS-12, EQ-5D-5L, STAI, and QIDS) will be analyzed using linear mixed models to assess within- and between-group effects over time. The primary analysis will follow an intention-to-treat principle, including all randomized participants in the groups to which they were originally assigned, regardless of adherence to the intervention protocol. A per-protocol analysis may be conducted as a secondary exploratory analysis. Missing data will be addressed using multiple imputation, assuming data are missing at random, and sensitivity analyses will be performed to assess the robustness of results.

As part of RQ5, the study also incorporates a comprehensive economic evaluation of the telerehabilitation system, which complements the clinical analyses and addresses a critical gap in MS rehabilitation research. A cost-utility analysis will be conducted to compare the telerehabilitation intervention and usual care, using incremental cost-effectiveness ratios derived from health care service use data and EQ-5D-5L–based quality-adjusted life years. Cost data will include implementation, infrastructure, maintenance, training, support services, and any differences in health service use or patient-reported outcomes. These data will be collected alongside the RCT to ensure alignment between clinical effectiveness and economic impact.

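### The RQ4 hypothesis (improvement among participants symptomatic at baseline) can be met by regression to the mean alone, and neither it nor RQ3's within-arm claim is tied to the randomised contrast

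*Protocol article*

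**What the plan says.** In the Protocol article, under Research and Innovation Questions, RQ4 is posed as a comparison: whether the telerehabilitation programme would "have a comparable effect on mood and quality of life (QoL) compared with standard physical therapy (facility based"). The hypothesis that follows is of another kind: "our hypothesis is that mood and QoL will be improved in participants whose symptoms are significant at baseline". It names no arm and no difference between arms.

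RQ3 has a two-part hypothesis. The first part is within-arm: "We hypothesize that both exercise intervention programs will improve mobility in people with MS". The second expects that "nonsignificant differences in mobility outcome measures between groups (telerehabilitation vs usual care) will be demonstrated".

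Under Outcome Measures for the Feasibility Multicenter RCT there are two assessments: "All outcome measures will be collected at baseline (at the initiation of the intervention program), and after the intervention period’s completion". Mood is measured with the STAI and QIDS and quality of life with the EQ-5D-5L. No cut-off for significant symptoms appears. Eligibility (Methodology, Approach, and Study Population) carries no mood or quality-of-life threshold, so any symptomatic subgroup has to be formed from baseline data.

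Under Data Analysis and Statistical Plan, the RQ3 and RQ4 outcomes "will be analyzed using linear mixed models to assess within- and between-group effects over time". That section does not say which of the two effects answers which hypothesis.

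**The concern.** A group picked because its baseline scores are poor contains more than its share of people measured on a bad day. Unless the retest correlation is perfect, its average moves back towards the overall mean at the second assessment, treated or not. A hypothesis of improvement in that group can therefore be confirmed by an inert programme, and in both arms at once. With only two assessments, change within an arm cannot be split into regression to the mean and effect.

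RQ3 has a related weakness through a different route. Its hypothesis expects no significant difference between arms, so its only positive evidence is that each arm got better. Repeating a performance test such as the 30STS, natural course, or the attention of being in a trial could all produce that. A gain shared by both arms also leaves the arms alike, so the whole predicted RQ3 pattern can appear with no treatment effect.

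The Methods overview promises preliminary efficacy on mobility, mental health and quality of life, and the Discussion expects the results to inform a fully powered RCT. A false signal here would feed that decision.

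**Working it through.** **Inputs from the article.** 24 participants per country in 4 countries: 24 × 4 = 96, which reproduces the stated total. There are two individually randomised groups. The allocation ratio is not stated; with 1:1 assumed, 96 / 2 = 48 per arm. There are two assessments. No power calculation is given, so there is none to reproduce.

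**Assumptions, not in the article.** Normally distributed scores with equal variance at both visits; retest correlation r from 0.6 to 0.9; 20%, 30% or 50% of participants symptomatic, defined on the outcome scale; no dropout; no true change.

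**Step 1, size of the spurious change (RQ4).** If a proportion p is selected above the cut-off c, the subgroup's mean baseline is φ(c)/p standard deviations above the overall mean, and the expected change with no effect is (1 − r) × φ(c)/p.

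- p = 20%: mean 1.40 SD. At r = 0.6, 0.4 × 1.40 = 0.56 SD.
- p = 30%: mean 1.16 SD. At r = 0.7, 0.3 × 1.16 = 0.35 SD.
- p = 50%: mean 0.80 SD. At r = 0.9, 0.1 × 0.80 = 0.08 SD.

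**Step 2, how often it looks significant.** 20,000 simulated trials per scenario, paired t-test in the selected subgroup, two-sided 5%, so nominally 2.5% in the direction of improvement:

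| Symptomatic | r | Spurious change (SD) | One arm of 48 | Arms pooled, 96 |
|---|---|---|---|---|
| 20% | 0.6 | 0.56 | 44.9% | 79.6% |
| 20% | 0.7 | 0.42 | 35.7% | 66.0% |
| 20% | 0.8 | 0.28 | 24.6% | 47.9% |
| 20% | 0.9 | 0.14 | 14.0% | 26.1% |
| 30% | 0.6 | 0.46 | 50.1% | 81.7% |
| 30% | 0.7 | 0.35 | 38.5% | 68.4% |
| 30% | 0.8 | 0.23 | 26.6% | 50.4% |
| 30% | 0.9 | 0.12 | 15.3% | 28.2% |
| 50% | 0.6 | 0.32 | 43.0% | 73.3% |
| 50% | 0.7 | 0.24 | 32.6% | 59.4% |
| 50% | 0.8 | 0.16 | 23.2% | 42.3% |
| 50% | 0.9 | 0.08 | 13.6% | 23.3% |

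**Step 3, the same subgroup compared between arms.** A two-sample t-test on change, telerehabilitation against comparator, gave a mean spurious difference of about 0 SD and a two-sided rejection rate of 4.8% to 5.3% in every scenario. Regression to the mean affects both arms equally and cancels.

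**Step 4, RQ3.** Take a gain of s standard deviations that has nothing to do with treatment and is common to both arms. The paired t-test in one arm has noncentrality s × √48 / √(2(1 − r)) on 47 degrees of freedom. For s = 0.2 and r = 0.8 this is 0.2 × 6.93 / 0.632 = 2.19, and the arm shows significant improvement with probability 0.574; both arms do so with probability 0.574² = 0.33. For r from 0.7 to 0.9, the probability that both arms improve significantly is 0.02 to 0.11 at s = 0.1, 0.17 to 0.74 at s = 0.2, and 0.56 to 0.99 at s = 0.3. The article gives no value for s, so these figures show only that the answer depends almost entirely on an unknown.

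**The case against.** The strongest reply is that the article plans no paired test in a symptomatic subgroup. It plans mixed models, by intention to treat, in all randomised participants, and the RQ4 sentence may be only an expectation. This stands in part: the rates above describe what happens if the hypothesis is tested as worded, not an analysis the article sets out. But a hypothesis is what an analysis plan is written to test. With two visits and complete data, a model that fits separate means by arm, visit and symptom group estimates the within-arm effect as the same mean change. Calling it a mixed model does not remove the bias.

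It is also fair that the article does not say the subgroup is formed on the outcome scale itself. If another measure is used, regression to the mean shrinks, though not to zero where the two correlate. And the trial is exploratory, with feasibility named in the Methods overview as its primary outcome; that limits the consequence but does not make a within-arm gain interpretable.

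Four stronger readings are tempting, and the documents do not support them:

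- *The randomised comparison is biased or pushed aside.* The analysis section names within- and between-group effects together and ranks neither. The between-group effect is planned and is free of this bias.
- *Regression to the mean also explains RQ3.* Nobody is selected on the 30STS or another mobility score for that hypothesis, so only practice, natural course and attention remain.
- *Self-reported baselines are taken after allocation is known.* Baseline is placed at the start of the programme; its order relative to disclosure of allocation is not stated, and an article commonly leaves that to the full protocol.
- *The analysis wastes precision by using change scores.* No change-score contrast is specified, and how the model treats baseline may properly be left to the statistical analysis plan.

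**Conclusion.** The point holds for the wording of the hypotheses. RQ4 asks a between-arm question and answers it with improvement in a baseline-symptomatic group, which regression to the mean produces whenever the retest correlation is below 1 and the subgroup is defined on the outcome or something correlated with it. The direction is firm. The size rests on assumed values for the correlation and the proportion symptomatic, on normal scores, on 1:1 allocation and on complete data, so the range should be quoted and not a single middle case.

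For RQ3 the conclusion is weaker. The hypothesis relies on within-arm change that has explanations other than treatment, but how large those are cannot be judged from the article. Both hypotheses share the remediable fault: the unbiased contrast is in the analysis plan, and neither hypothesis is attached to it. This should be corrected before the RCT starts, but it does not invalidate the trial.

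**What to change.** Restate the RQ3 and RQ4 hypotheses as the baseline-adjusted difference between arms at the end of the 10-week intervention, with a confidence interval, in all randomised participants. For RQ4, examine the role of baseline symptoms through an arm-by-baseline-score interaction in the whole sample instead of a selected subgroup, and label it exploratory at 96 participants. Report within-arm changes descriptively, with no efficacy claim. In the analysis section, say that the between-group effect answers RQ3 and RQ4.

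The cost is a change of wording and no new data. According to the article, the RCT is planned for January 2026 and its ethics applications were still to be submitted, so the change can go in with them. What is lost is the claim that each programme, or the symptomatic group, improved. Where the comparator is itself physical therapy, as RQ3 and RQ4 frame it, the between-arm difference shows how the programmes compare and not whether either beats no treatment; the text should say so.

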### Methodology, Approach, and Study Population

The different WPs of the research project and timeline are presented in Figure 1 and Table 1. The first phase of this project will examine the system usability and feasibility of an innovative advanced telerehabilitation system in people with MS (WP2). The system usability and feasibility study will be conducted in each participating country (Israel, Italy, Ireland, and Denmark) with a small group of people with MS (n=10 per center) with varying disability. Participants will be recruited according to the following criteria: aged 18 years or older; confirmed diagnosis of MS based on the McDonald criteria [30] (both relapsing-remitting and progressive MS); an Expanded Disability Status Scale (EDSS) score of 2.5-6.5; willing to travel to the local study site for the evaluation sessions; and internet service, and having a device (eg, smartphone, tablet, or PC) equipped with a camera that meets the technical specifications recommended by the telerehabilitation system manufacturer. Individuals who have had a documented relapse during the past 3 months will be excluded, as will those who are unable to follow simple instructions.

Following assessment and exercise prescription, participants will complete an exercise program delivered by the telerehabilitation system. The short-term program will include 8 exercise training sessions (45- to 60-minute sessions twice weekly for 4 weeks). The amount of training throughout the short-term program will be sufficient for collecting data and taking note of the safety, usability, and feasibility of the advanced rehabilitation technologies [31]. The primary outcome measure of WP2 will be collected at the end of the short-term telerehabilitation exercise program with the Telehealth Usability Questionnaire (TUQ) [32], a solid, robust, and versatile tool used to measure the quality of the telehealth system’s interaction and services. In addition, qualitative data will be collected through semistructured interviews with key stakeholders (people with MS and therapists) and analyzed thematically.

In parallel with the system feasibility and usability study, we plan to develop and psychometrically test a set of remote balance and functional mobility tests delivered via the telerehabilitation system (WP3). We will adapt and manualize 5 remote mobility tests that are collected through the telerehabilitation system: the 30-second sit-to-stand (30STS) test, timed-up-and-go (TUG) test, functional reach test (FRT), 20-second single-leg stance (20SLS) test, and the Short Physical Performance Battery (SPPB). The SPPB includes the following tests: side-by-side stand (10 seconds), semitandem stand (10 seconds), tandem stand (10 seconds), a gait speed test over 3 meters, and a 5-time repeated chair stand test. Upon completion of the developmental phase, we will conduct a test-retest reliability study for in-person and telehealth data capture and a criterion validity study comparing telehealth and in-person data with 15 people with MS (EDSS 2.5-6.5) at each site (n=60).

To examine the efficacy of the advanced telerehabilitation solution for people with MS, we propose an international feasibility multicenter RCT (WP4). We will include a target sample of 24 participants per country (in 4 countries; 96 participants in total) based on the stepped rule of thumb proposed by Whitehead et al [33], who estimated the optimal sample size for an early-stage/pilot RCT to be 24. Importantly, as the results may differ across countries, we consider each country an individual site for the feasibility RCT. Statistical analysis will be performed for the total group and each country separately. The participants will be randomly allocated (individual randomization) into one of two groups: (1) home-based telerehabilitation exercise training via the WizeCare platform [28] or (2) usual care. The sample criteria for the feasibility multicenter RCT will be the same as those for WP2.

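### Analysing WP4 separately in each country does not assess whether the treatment effect differs between countries, and at about 12 per arm the country results will often disagree by chance

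*Protocol article*

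**What the plan says.** The section Methodology, Approach, and Study Population of the protocol article sets the size of WP4: "We will include a target sample of 24 participants per country (in 4 countries; 96 participants in total". The figure of 24 comes from a published rule of thumb, attributed to authors "who estimated the optimal sample size for an early-stage/pilot RCT to be 24". The article then gives its reason for looking at countries individually, "as the results may differ across countries, we consider each country an individual site for the feasibility RCT", and follows it directly with the analysis commitment: "Statistical analysis will be performed for the total group and each country separately".

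Data Analysis and Statistical Plan says that the outcomes for RQ3 and RQ4 "will be analyzed using linear mixed models to assess within- and between-group effects over time". It neither links this model to the country analyses nor says how they are to be read. The Discussion describes the trial as exploratory, its conclusions as provisional, and its sample as possibly too small for small effects.

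**The concern.** The reason and the method do not match. If effects may differ between countries, the quantity of interest is the difference between country-specific effects. A separate analysis in Denmark asks only whether the arms differ in Denmark. Four such analyses, set side by side, invite the reader to infer heterogeneity from the fact that one p-value is below 0.05 and another is not. That comparison has no controlled error rate.

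The question itself is legitimate. Under Intervention and Comparators the article acknowledges that usual care is not the same thing in every country, so the contrast between arms could well vary. With about 24 people per country, however, the separate results will be noisy enough to suggest differences that do not exist, or to hide ones that do. Sites, or the planners of the later full-scale trial, could act on such patterns.

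**Working it through.** **Inputs from the article.** 24 participants per country, 4 countries, two arms, individual randomisation, and an analysis of the total group and of each country.

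**Assumptions, because the article gives no figure.** 1:1 allocation, two-sided 0.05, no dropout. Effects are in SD units. Unadjusted figures compare post-treatment means. Adjusted figures condition on baseline with an assumed baseline–post correlation ρ of 0.5 to 0.7, which multiplies the standard error by √(1 − ρ²).

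**The plan's own figure.** 24 × 4 = 96, which reproduces. The 24 is a rule of thumb with no stated effect, SD, alpha or power, so there is no power claim to reproduce.

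**Precision in one country.**
- Per arm: 24 / 2 = 12.
- SE = √(2/12) = 0.408 SD. Adjusted: 0.408 × √0.75 = 0.354 (ρ = 0.5) and 0.408 × √0.51 = 0.292 (ρ = 0.7).
- Unadjusted 95% CI half-width: 2.074 × 0.408 = 0.85 SD.

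**Power in one country at 0.5 SD** (noncentral t).
- Unadjusted: noncentrality 0.5 / 0.408 = 1.22 on 22 df, power 21.6%.
- Adjusted: noncentrality 1.41 to 1.72 on 21 df, power 27% to 37%.
- Effect giving 80% power: 1.20 SD unadjusted, about 1.04 to 0.86 SD adjusted.

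**Apparent disagreement when all four countries share the same 0.5 SD effect.** With power p per country, the probability that some are significant and others not is 1 − p⁴ − (1 − p)⁴.
- Unadjusted, p = 0.216: 1 − 0.002 − 0.378 = 62%.
- ρ = 0.5, p = 0.271: 1 − 0.005 − 0.282 = 71%.
- ρ = 0.7, p = 0.373: 1 − 0.019 − 0.154 = 83%.

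Baseline adjustment makes this worse at 0.5 SD, because it moves power from low towards the middle, where mixed results are most likely.

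**At least one of four estimates with the wrong sign, same 0.5 SD effect.** Per country Φ(−0.5/SE); any of four 1 − (1 − that)⁴.
- Unadjusted: Φ(−1.22) = 0.110, any of four 37%.
- ρ = 0.5: 0.079, any of four 28%. ρ = 0.7: 0.043, any of four 16%.

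**No effect in any country.** P(at least one of four with p < 0.05) = 1 − 0.95⁴ = 18.5% for one outcome.

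**The alternative on the same 96 participants.**
- Total group, 48 per arm, unadjusted: 95% CI half-width 0.41 SD; 80% power at 0.58 SD.
- Treatment-by-country test: F on 3 and 88 df, noncentrality 6 × Σ(δᵢ − δ̄)², where 6 = 1/(2/12). If one country has a 0.5 SD effect and three have none, Σ = 0.1875, noncentrality 1.125, power 12%. If two have it, Σ = 0.25, noncentrality 1.5, power 15%. At 1.0 SD the corresponding powers are 38% and 50%.

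The interaction test asks the right question but is weak at this size. Estimates with intervals should therefore carry the country results.

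**The case against.** The best defence is that this is an exploratory feasibility trial with a total-group analysis, that the article attaches no confirmatory claim to any country result, and that seeing each site's data is a sensible aim where usual care differs. The article also does not say in so many words that the separate analyses are meant to test for country differences. Most of this stands, and it limits the harm to over-interpretation. It does not remove the mismatch: the possibility of differing results introduces the country analyses, nothing labels them descriptive, and the general caveat about small effects does not warn that a country analysis would usually miss 0.5 SD.

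A second objection is that unadjusted figures are pessimistic, since baseline is measured and a mixed model is planned. That is fair for power and for wrong signs, so ranges are shown. For disagreement in significance at 0.5 SD, adjustment goes the other way.

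A third is that the interaction test is too weak to help. It is weak, which is a reason to report descriptive country estimates and not to rely on any test, pooled or separate.

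Stronger readings are tempting, but the article does not support them:
- **Allocation is not balanced by country.** The article says only "The participants will be randomly allocated (individual randomization) into one of two groups". That rules out cluster allocation, not stratification or blocking, and a condensed article commonly leaves such detail to the full protocol.
- **The pooled analysis ignores country.** No covariates of any kind are listed for the mixed models, so silence about a country term shows nothing.
- **Every listed outcome will be significance-tested in every country.** The article speaks of statistical analysis by country without saying this, so the error rate above is given for one outcome only.
- **Country-level nonsignificance would confirm RQ3.** How RQ3 treats nonsignificance is a separate issue that affects the total-group analysis equally.

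**Conclusion.** The point holds as a badly fixed analysis choice of moderate weight. The separate country analyses cannot show whether the treatment effect differs between countries, and significance will disagree by chance in most realisations of a common 0.5 SD effect: 62% unadjusted, 71–83% with baseline adjustment. Power per country at that effect is 22% (27–37% adjusted), and the chance of at least one reversed sign is 37% (28–16% adjusted). These figures rest on 1:1 allocation, two-sided 0.05, no dropout and, for the adjusted values, an assumed correlation of 0.5 to 0.7; none of these is stated in the article. Dropout would lower the per-country power further. The total-group analysis is not undermined.

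**What to change.** Replace the sentence on country analyses in Methodology, Approach, and Study Population with wording such as: *The treatment effect will be estimated in one model on all 96 participants with country as a factor. Variation between countries will be assessed with a treatment-by-country term, recognising its low power. Country-specific estimates with 95% confidence intervals from this model will be shown descriptively; no separate significance tests will be done and no conclusions drawn within countries.* If baseline and post-treatment values are both modelled as outcomes, the relevant term is group by time by country.

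The cost is one sentence and no additional participants. The article plans WP4 for January 2026, with its ethics applications still to be submitted, so the change can be made before data exist. The downside is that individual sites lose a stand-alone p-value; they keep an estimate and an interval.

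### WP4 takes over the WP2 eligibility criteria unchanged, so people who completed the WP2 platform training can be randomised, which could make the feasibility estimates unrepresentative of new users

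*Protocol article*

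**What the plan says.** The section Methodology, Approach, and Study Population of the protocol article sets the WP4 eligibility rule in one sentence: "The sample criteria for the feasibility multicenter RCT will be the same as those for WP2". The WP2 list, earlier in that section, asks for adults with confirmed MS, an EDSS score of 2.5-6.5, willingness to travel to the site, internet access and a suitable camera device. Its exclusions are these: "Individuals who have had a documented relapse during the past 3 months will be excluded, as will those who are unable to follow simple instructions".

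WP2 is run in each of the four countries "with a small group of people with MS (n=10 per center) with varying disability". On exposure, the article says: "The short-term program will include 8 exercise training sessions", given twice weekly over 4 weeks. WP4 then recruits 24 people in each of the same four countries and randomises them individually to the platform programme or usual care. It analyses the total group and each country separately.

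The Overview names trial feasibility as the primary outcome of WP4, and the Discussion says the results should inform a fully powered trial. Under Outcome Measures, baseline digital literacy is collected as a possible confounder. Prior use of the platform is not mentioned.

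**The concern.** An exclusion for having taken part in WP2 cannot be among WP2's own entry criteria. Declaring the WP4 criteria identical therefore admits WP2 completers. This is a consequence of a stated rule and not only of something left unsaid.

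Overlap is plausible. Countries and criteria are the same, and WP2 completers are already known to the sites and equipped with a device. The Gantt chart runs WP2 through Q5 and starts WP4 in Q6. The Results section puts the two starts about nine months apart (April 2025 and January 2026).

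Two things are at stake:

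- **Feasibility.** People who come back after 8 sessions are plausibly those who tolerated the system. Their adherence and acceptance need not resemble those of the new users whom a later trial would enrol. Balance between arms does not cure this.
- **The contrast.** If part of the benefit has already been gained, the difference between arms could be smaller. In a country sample of 24, a few such people could also fall unevenly between the arms.

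**Working it through.** **Inputs from the article (Methodology, Approach, and Study Population).** WP2: 10 per country. WP4: 24 per country. Four countries.

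**Assumption.** The allocation ratio is not given in the article, so 1:1 is assumed: 12 per arm within a country and 48 per arm overall.

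**Step 1, the plan's own totals.** 4 × 24 = 96 for WP4, as stated. 4 × 10 = 40 for WP2, as the Abstract states.

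**Step 2, ceiling on overlap.** If every WP2 participant re-enrolled: 10/24 = 41.7% per country, and 40/96 = 41.7% overall, with about 20 in each arm of 48. This is an upper limit, not an expected value.

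**Step 3, effect on adherence (illustration).** Observed adherence = (1 − f) × a₀ + f × a₁, where f is the share of WP2 completers, a₀ adherence in new users and a₁ adherence in returning users. The documents give neither a₀ nor a₁, so two assumed pairs are shown.

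- a₀ = 70%, a₁ = 90%: with 10, 20 or 40 of 96 returning (f = 0.104, 0.208, 0.417), observed adherence is 72%, 74% or 78%.
- a₀ = 60%, a₁ = 95%: 64%, 67% or 75%.

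**Step 4, dilution of the contrast (illustration).** Proportional loss = f × r, where r is the share of the treatment effect no longer available in returning users. The documents give no value for r.

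- 10 returning: 0.104 × r, a loss of 2.6% at r = 0.25, 5.2% at r = 0.5 and 10.4% at r = 1.
- 20 returning: 5.2%, 10.4% and 20.8%.
- 40 returning: 10.4%, 20.8% and 41.7%.

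**Step 5, chance imbalance within a country.** With m WP2 completers among 24 and 12 allocated to each arm, the number in usual care is hypergeometric.

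- At least one in usual care: 1 − C(24 − m, 12)/C(24, 12). This is 50%, 76%, 98% and about 100% for m = 1, 2, 5 and 10.
- A 4-1 or 5-0 split in either direction when m = 5: 2 × [C(12,5) + C(12,4) × 12]/C(24,5) = 2 × (792 + 5,940)/42,504 = 32%.

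**Step 6, after the fix.** WP2 completers in WP4 fall to 0 of 96. The sample size does not change.

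**The case against.** The strongest reply is that this is a condensed article. It nowhere says that earlier participants will be re-enrolled, and the WP4 ethics applications are still to be submitted, so the full protocol may carry the exclusion. That stands as a limit on what can be claimed: whether the problem occurs, and how large it is, cannot be known from this text. It does not remove the point, because an added exclusion would contradict the sentence that makes the criteria the same.

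Several stronger readings are tempting, and the documents do not support them.

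- **Contamination of usual care.** A reader might infer this because pre-trained people can be allocated to that arm. But WP2 exposure precedes individual randomisation and is balanced between arms in expectation. Outcomes are also measured at WP4 baseline, so gains retained from WP2 are already in the baseline of both arms. What remains is possible dilution, reduced generalisability and chance imbalance.
- **WP3 as a second source of contamination.** A reader might add the 60 WP3 participants to the 40 from WP2 and set 100 people against 96 places. WP3 gives mobility tests and not training, and any practice effect on the shared tests (30STS, SPPB, FRT) falls on both arms. It bears at most on familiarity with the system.
- **A push towards no difference.** The article hypothesises nonsignificant differences between groups, and dilution would help that along. But better adherence among returning users in the platform arm could enlarge the contrast, so the net direction is unknown.
- **Having already received the tested intervention.** WP2 is a 4-week programme. WP4 is a 10-week individualised one, run after any system upgrades that follow from WP2.

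It is also fair that the article does not name recruitment and dropout as WP4 outcomes. The Gantt chart lists adherence and satisfaction for WP4, and the argument needs only these.

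**Conclusion.** The point holds in a limited form. As written, WP2 completers are eligible for WP4, up to 10 of 24 per country. If some re-enrol, WP4 adherence and acceptance could describe experienced users in part, when the aim is to plan a trial in new ones. The contrast could be diluted, or prior exposure could be split unevenly within a country.

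The only sizes that follow from the documents are the ceilings. The adherence and dilution figures rest on assumed values, and the imbalance figures rest on 1:1 allocation and an assumed number returning. A reader might take 41.7% overlap or a 21% loss of effect as the expected harm. The first requires every WP2 participant to return, and the second multiplies that by an assumed halving of the effect.

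The change is still worth making before WP4 starts: the rule is explicit, feasibility is a stated primary outcome, and the repair is one line.

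**What to change.** Replace the sentence that equates the criteria with one stating that WP4 uses the WP2 criteria plus one further exclusion: prior participation in the WP2 training programme. Do this before the WP4 ethics applications are submitted.

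For WP3 participants, record prior exposure at baseline and report the feasibility estimates with and without them. Stratifying on exposure is not needed and would leave very sparse strata with 24 per country. A wider ban on any earlier use of the platform is not needed either, and would also remove users from outside the project.

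The cost is up to 10 fewer candidates per country (40 in all), one baseline item and one additional set of feasibility summaries. The target of 96 is unaffected.
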